#### Evaluation of retinal vessels

Retinography will be performed using a Topcon TRC NW 200 non-mydriatic retinal camera (Topcon Europe B.C., Capelle a/d Ijssel, The Netherlands), obtaining nasal and temporal images centred on the disk. The nasal image with the centred disk will be loaded into the developed software, AV Index calculator (Ciclorisk SL, Salamanca, Spain, registry number 00/2011/589). This software automatically recognises and draws two external concentric circles that delimit area A, 0–0.5 disk diameters from the optic disk margin, and area B, 0.5–1 disk diameters from the margin. The software first identifies the limits of the different vessels, after which it automatically recognises arteries and veins, and makes multiple measurements of the diameter of the section of vessels circulating through area B. It finally estimates the mean calibre of veins and arteries in millimetres, and these measurements are summarised as an arteriole–venule ratio, arteriovenous index (AVIx). An AVIx of 1.0 suggests that arteriolar diameters are on average the same as venular diameters in that eye, whereas a smaller arterio-venous ratio (AVR) suggests narrower arterioles. The pairs of main vessels in the upper and lower temporal quadrants will be used, rejecting all other vessels, to improve reliability and increase efficiency of the process, analysing measures for each quadrant separately and together to estimate the mean measure in each eye.

#### Coronary artery calcium score

Coronary calcium will be quantified using a 256-slice multidetector CT scanner (Brilliance iCT, Philips) according to the Agatston *et al*^84^ method, with the support of specific programming and specialised software (Intellispace Portal, Philips). This technology is the latest in the sector, allowing coronary calcium to be estimated with radiological exposures <1 mSv, equivalent to performing a spinal X-ray.

#### Renal assessment

Kidney damage will be assessed by measuring the estimated glomerular filtration rate using the Chronic Kidney Disease Epidemiology Collaboration (CKD-EPI)^85^ equation and proteinuria, as assessed by the albumin–creatinine ratio, following the criteria of the 2013 European Society of Hypertension/European Society of Cardiology Guidelines.^62^ Subclinical organ damage will be defined as glomerular filtration rate below 30–60 mL/min/1.73 m^2^ or microalbuminuria (30–300 mg/24 hours), or albumin–creatinine ratio (30–300 mg/g; 3.4–34 mg/mmol; preferably on morning spot urine). Renal disease will be defined as glomerular filtration rate <30 mL/min/1.73 m^2^ (body surface area), proteinuria (>300 mg/24 hours) or albumin–creatinine ratio >300 mg/24 hours.^62^

#### Cardiac assessment

ECG examination will be performed using a General Electric MAC 3.500 ECG System (Niskayuna, New York, USA), which automatically measures wave voltage and duration and estimates the criteria of the Cornell voltage-duration product (VDP).^86^ ECG left ventricular hypertrophy will be defined as a Sokolow-Lyon index >3.5 mV; R wave in Left arm (RaVL)>1.1 mV or Cornell VDP>244 mV×ms.^62^

#### Laboratory measurements

Venous blood sampling will be performed between 08:00 and 09:00 after participants have fasted and abstained from smoking and consumption of alcohol and caffeinated beverages for 12 hours. Fasting plasma glucose, creatinine, uric acid, Ca, P, serum total cholesterol, high-density lipoprotein cholesterol and triglyceride levels will be measured using standard enzymatic automated methods. Low-density lipoprotein cholesterol will be estimated by the Friedewald equation when the direct parameter is not available. Glycated haemoglobin will be measured with an immune-turbidimetric assay. Detection of 25-hydroxyvitamin D by immunoassay technical. High-sensitivity C reactive protein levels and fibrinogen concentrations will be determined by an immune turbidimetric assay. Cytokine (interleukin 1β, TNF-α) concentrations in plasma will be determined by ELISA using commercial kits and following the manufacturer's recommendations. Oxidative stress will be determined by measuring lipid peroxides (thiobarbituric acid reactive substances (TBARS), using a colorimetric technique using commercial kits) and nucleic acid derivatives (8-hydroxy-2-deoxyguanosine) by ELISA using commercial kits and following the manufacturer’s recommendations.

*Telomere length*: Telomere length will be measured using the real-time PCR technique. This is a technique that allows one to quantify the initial amount of DNA in a given fragment comparing this amplification with another performed simultaneously. To analyse these relative changes, a reference fragment in the DNA is chosen as the standard. In our study, we will use as the endogenous single copy control gene: 36b4. PCRs will be performed on 96-well optic plates (Micro Amp Fast Optical 96-Well reaction plate with Barcode 0.1 mL, Applied Biosystems). On each plate, two different reactions will be performed for each sample in different wells: an amplification reaction of telomeres and another amplification reaction of the 36b4 gene. In turn, we perform three replicates of each amplification to minimise the variability in concentration of the samples. In total, we will perform 9 PCRs for each patient. To amplify the 36b4 gene, we will use the primers: 36b4 F: 5′-CAGCAAGTGGGAAGGTGTAATCC-3′ and 36b4R: 5′-CCCATTCTATCATCAACGGGTACAA-3′; and to amplify the telomeres, we will use the primers TelF: 5′-GGTTTTTGAGGGTGAGGGTGAGGGTGAGGGTGAGGGT-3′ and TELR: 5′-TCCCGACTATCCCTATCCCTATCCCTATCCCTATCCCTATCCCTA-3′.

Blood samples will be collected in the primary care centre, and will be analysed at the University Hospital of Salamanca in external quality assurance programmes of the Spanish Society of Clinical Chemistry and Molecular Pathology.

People who perform the different tests will be blinded to the clinical patient data. All parameter assessments will be made within 10 days.

### Statistical analysis

Data input will be performed using the Teleform system (Autonomy Cardiff Vista, California, USA), with a questionnaire previously designed for the project. Normal distribution of variables will be verified using the Kolmogorov-Smirnov test. Quantitative variables will be displayed as mean±SD if normally distributed or as the median (IQR) if asymmetrically distributed, and qualitative variables will be expressed as frequencies. Analysis of difference of means between variables of two categories will be carried out using a Student’ t-test or a Mann-Whitney U test, as appropriate, while qualitative variables will be analysed using a χ² test. To analyse the relationship between qualitative variables of more than two categories and quantitative variables, an analysis of variance and the least significant difference test will be used in the post hoc tests; a Kruskal-Wallis test will be used in cases where the variables are not normally distributed. The relationship of quantitative variables to each other will be tested using Pearson or Spearman correlation as appropriate. Analysis of covariance (ANCOVA) will be performed to adjust for the variables that can affect the results as confounders. A multivariate analysis of variance (MANOVA) will be performed in cases with more than one dependent variable to identify whether changes in the independent variables have significant effects on the dependent variables. The association between the variables studied (PWV and CAVI with the independent variables analysed)) will be performed by multiple linear regression. Factors associated with the presence or absence of EVA will also be analysed by logistic regression. Data will be analysed using the SPSS V.23.0 statistical package (SPSS Inc, Chicago, Illinois, USA). A value of p<0.05 will be considered statistically significant. Statistical analysis of the extent of telomere length will be performed with the programs Step One 2.1 software (Applied Biosystems) and Enterprise GenEx 5.2.1.

To minimise the risk of bias resulting from foreseeable losses in the study, we will apply a process of multiple imputation to the original database, using the chained equations method proposed by van Buuren *et al*.^87^ Fifty files will be generated from this method, in which missing values will be replaced by their corresponding imputed values. Estimators obtained from each file will be combined by the method of Rubin.^88^ These processes will be carried out by the Ice^88^ and Mim programs, updated to V.14 of the statistical package Stata.

The statisticians/researchers who perform the different analyses will be blinded to the clinical patient data.

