## Introduction

The process of population ageing that is occurring in developed societies represents a major challenge for the health system. Cardiovascular diseases (CVD) are the most common cause of morbidity and mortality in the world, representing half of the deaths in persons aged over 65 years and affecting >70% of patients with diabetes mellitus. The non-modifiable cause of vascular ageing in healthy adults is age, because it causes increased arterial stiffness and changes in chromosome replication with telomere shortening.^1^
^2^

The comparison of biological age with chronological age allows us to establish if the pattern of vascular ageing is at an expected or accelerated rate, that is, if early vascular ageing (EVA) is present or not.^1^
^2^

*Arterial stiffness and ageing*: Arterial stiffness increases with age even in healthy adults.^3^ It involves changes in vascular structure with thickening of the arterial wall, changes in vascular function due to increased stiffness, and decreased wall distensibility of large arteries, associated with endothelial dysfunction and pulse wave changes.^3^
^4^ These changes are primarily mediated by nitric oxide.^1^ Arterial ageing is a multifactorial process associated with changes in structure and function of the large arteries.^1^ These changes are related to age, and are accelerated in the presence of associated CVD,^5–9^ cardiovascular risk factors or cardio-unhealthy lifestyles.^10^ Some of these factors are controllable, and a greater understanding of the links existing between vascular ageing, lifestyle and CVD will help find strategies geared to preventing or delaying this ageing.^11^
^12^

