### Sample size

The sample size was estimated to find a difference of 0.60 points in the 14-item questionnaire on adherence to a Mediterranean diet between participants with EVA and those without. We used this variable because we think that it, of all the variables, varies the least over time. Assuming a 1:3 ratio between participants with and without EVA as the most unfavourable situation, accepting an α risk of 0.05 and a β risk of 0.20 in a two-sided test, and assuming a rate of losses due to technical difficulties or refusal to participate of 10%, 488 participants would be required, 122 in the first group and 366 in the second. It is assumed that the common SD is 1.94 points. Five hundred participants will be selected.

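### Student's t-test is named for the EVA contrast planned at 1:3, and LSD for age-group pairs, with no protection against unequal SDs; Welch-type tests would remove this at almost no cost (minor)

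*Protocol article*

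**What the plan says.** The Statistical analysis section of the protocol article sets one rule for all two-group comparisons of quantitative variables: "Analysis of difference of means between variables of two categories will be carried out using a Student’ t-test", with the Mann-Whitney U test as the alternative, as appropriate. For more than two groups it names analysis of variance with LSD post hoc tests, or Kruskal-Wallis for non-normal variables. Normality is to be checked with the Kolmogorov-Smirnov test. No check of variances and no unequal-variance test is named. The threshold is the usual one: "A value of p<0.05 will be considered statistically significant".

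The Sample size section plans the contrast between participants with and without EVA: "Assuming a 1:3 ratio between participants with and without EVA as the most unfavourable situation". It gives 122 and 366 participants, and for the diet score "It is assumed that the common SD is 1.94 points".

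The Study population section fixes five age groups of 100, each with 50 men and 50 women. The main analyses of pulse wave velocity, CAVI and EVA status are multiple linear and logistic regression.

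**The concern.** Student's t-test estimates one SD from both groups together. With equal group sizes, a difference between the two SDs hardly changes the error rate. At 1:3 it does. If the smaller group is the more variable, the standard error is too small and the test rejects too often. If the smaller group is the less variable, the standard error is too large and real differences are missed.

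The section applies the same test to diet, psychological, inflammatory and laboratory variables, while a common SD is assumed for the diet score only. A check for normality does not detect unequal SDs.

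LSD has a related weakness. Each pair of age groups is compared using one SD pooled over all five groups, so equal group sizes do not protect an individual pair.

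What is at stake is the error rate of the unadjusted EVA v no-EVA comparisons and of the age-group pairs.

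**Working it through.** **1. The plan's own figure.** Inputs from the Sample size section: "The sample size was estimated to find a difference of 0.60 points in the 14-item questionnaire", SD 1.94, "accepting an α risk of 0.05 and a β risk of 0.20 in a two-sided test", ratio 1:3, losses 10%.

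- Normal approximation for the smaller group: n = (1 + 1/3) × (1.94 × (1.960 + 0.842)/0.60)² = 109.4, so 4 × 109.4 = 437.6 in total.
- With the t-distribution: 110 + 329 = 439, and 439/0.90 = 487.8, so 488. The stated total is reproduced. It rests on a common SD.

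**2. Error rate of the pooled t-test.** Let p be the share with EVA, q = 1 − p, and r = SD(EVA)/SD(no EVA). In large samples the variance the test uses, divided by the true variance of the difference, is

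k = (p r² + q)/(q r² + p),

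and the actual two-sided error is 2 × (1 − Φ(1.96 × √k)). The ratios r are assumptions, because the documents give none.

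| r | k at p = 0.25 (122 v 366) | error | k at p = 0.35 | error |
|---|---|---|---|---|
| 0.67 | 1.476 | 1.7% | 1.261 | 2.8% |
| 0.8 | 1.247 | 2.9% | 1.141 | 3.6% |
| 1.0 | 1.000 | 5.0% | 1.000 | 5.0% |
| 1.25 | 0.802 | 7.9% | 0.876 | 6.6% |
| 1.5 | 0.677 | 10.7% | 0.793 | 8.1% |

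For r = 1.5 at 1:3: k = (0.5625 + 0.75)/(1.6875 + 0.25) = 0.677; 1.96 × √0.677 = 1.613; error 10.7%.

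Simulation with normal data at 122 v 366 (20,000 runs per ratio) gave 1.6%, 2.7%, 5.0%, 7.9% and 10.9% for Student's test. Welch's test on the same data gave 4.8% to 5.1%.

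The 35% column is shown because EVA means exceeding the 75th centile on either measure or both. If both centiles are taken over the whole sample, the share with EVA is 25% when the two measures are perfectly correlated and about 44% when they are uncorrelated; 35% corresponds to a correlation of 0.7. These correlations are also assumptions.

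**3. Balanced comparisons.** At p = 0.5, k = 1 for every r, so the gender comparison (250 v 250) stays at 5%; simulation gave 4.9% to 5.3% for ratios 0.5 to 2. The overall analysis of variance on five groups of 100 ran at 5.4% with the SD rising 1.5-fold from youngest to oldest, and 5.7% with a 2-fold rise.

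**4. LSD pairs.** Assume SDs of 1, 1.125, 1.25, 1.375 and 1.5 across the five age groups. The pooled variance is (1 + 1.266 + 1.563 + 1.891 + 2.25)/5 = 1.594.

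- Youngest pair: own mean variance (1 + 1.266)/2 = 1.133; k = 1.407; 1.96 × √k = 2.325; error 2.0%.
- Oldest pair: (1.891 + 2.25)/2 = 2.070; k = 0.770; 1.96 × √k = 1.720; error 8.5% (8.2% in simulation).

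**5. Cost of Welch's test if the SDs are equal.** At 110 v 330 and a standardised difference of 0.60/1.94 = 0.309, Student's test has 80.0% power on 438 degrees of freedom. Welch's test has about 187 degrees of freedom and 79.8% power. Simulation gave 80.1% and 79.9%. Both put the loss at about 0.2 points.

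**The case against.** A good deal can be said for leaving the plan alone.

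- **No evidence of unequal SDs.** Under the plan's own common SD the t-test runs at 5%. This stands: every departure above is conditional on an assumed ratio.
- **1:3 is the worst case.** The plan says so, and a larger EVA share shrinks the effect, as the 35% column shows. It does not remove it.
- **The main models are regressions.** Logistic regression makes no equal-variance assumption, and the effect on linear regression was small in simulation, about 6% to 7%. So only unadjusted comparisons are materially touched. This stands and limits the weight of the point.
- **For stiffness by age the null is already thought false.** The Introduction says arterial stiffness rises with age, so a false-positive rate between neighbouring age groups matters less there. This is fair, although LSD is named for any quantitative variable.
- **A condensed article may leave the t-test variant to the full plan.** This carries less weight, because the article names specific tests; the suggestion is a better choice in their place.

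A reader might also infer that unequal spread is built into the concept of EVA. The Introduction says that comparing biological with chronological age "allows us to establish if the pattern of vascular ageing is at an expected or accelerated rate", and if people age at different rates their values might fan out. The documents do not support that step. They describe the level of stiffness and a classification of people, and say nothing about spread by age or by EVA status. Even if the spread of stiffness did grow with age, it would not follow that diet, anxiety or cytokine values vary more in the EVA group, and those are the variables compared at up to 1:3.

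**Conclusion.** The point holds as a minor, conditional improvement. The plan names a pooled-variance t-test for a contrast planned at up to 1:3 and checks only normality. For assumed SD ratios of 0.67 to 1.5, the nominal 5% test would run at 1.7% to 10.7% at 122 v 366, or 2.8% to 8.1% if 35% have EVA. LSD pairs would run at about 2% and 8.5% if the SD rose 1.5-fold across the age groups. The balanced gender test and the overall age-group analysis of variance are not a concern.

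It would be wrong to read these ranges as the error rates the study will have. They show how far the tests could drift, in either direction, under ratios the documents neither state nor exclude.

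**What to change.** In the Statistical analysis section, replace Student's t-test by Welch's test for two-group comparisons of means, and replace the LSD test by an unequal-variance post hoc test (Games-Howell). The Mann-Whitney and Kruskal-Wallis alternatives can stay. Heteroscedasticity-robust (HC3) standard errors in the linear models for pulse wave velocity and CAVI are optional, since the effect there is small.

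No change to the data, sample size or design is needed. Welch's test costs about 0.2 percentage points of power if the SDs are equal. The remaining work is to specify the new tests and to check how they are run on the fifty imputed files.

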### Quality control

Different processes will be carried out to guarantee the study data quality and thus maximise the validity and reliability of measurements of the results. To this effect, field work operation manuals have been prepared. These documents specify the adequate procedure for performing each test. Educational leaflets will be developed to ensure adequate pressure measurement by patients at home. All of these actions will confirm adequate performance of each procedure. Monthly meetings will be held with the principal investigator of the study to analyse the entire process, and an annual report on study progress will be prepared.

#### Project schedule

This project will be performed in 3 years, with the aim to analyse factors that have an influence on EVA, estimated by cf-PWV and Cardio Ankle Vascular Index (CAVI), and to determine differences by gender in a Spanish population. During the first 2 years, the collection of data questionnaires, sample selection and inclusion should be developed and all the necessary information gathered. During the third year, the analysis and dissemination of the results will be performed.

## Dissemination

Participants will be required to sign an informed consent form prior to inclusion in the study, in accordance with the Declaration of Helsinki^89^ and the WHO standards for observational studies. The study has been registered in ClinicalTrials.gov with identifier NCT02623894. Participants will be informed of the objectives of the project and of the risks and benefits of the examinations made. None of the examinations pose life-threatening risks for the type of participants to be included in the study. The study includes the obtaining of biological samples; the study participants therefore will be informed in detail. The confidentiality of the recruited participants will be ensured at all times in accordance with the provisions of current legislation on personal data protection (15/1999 of 13 December Protection of Personal Data Official Law (LOPD)), and the conditions contemplated by Act 14/2007 on biomedical research.

### Dissemination plan

We will use a variety of methods to ensure that our work will achieve maximum visibility. Publication of our study protocol provides an important first step in this direction. In this paper, we have sought to offer a comprehensive overview of the relevant literature, while underlining current research gaps that necessitated the design and implementation of the EVA study.

Similarly, the study results, given their applicability and implications for the general population, will be disseminated in research meetings and in at least five articles published in scientific journals.

## Discussion

Numerous studies^5–9^ have analysed the factors influencing vascular stiffness, finding that arterial ageing is related to changes in the mechanical and structural properties of the vascular wall, which lead to loss of arterial elasticity and reduced distensibility. However, to what extent these changes occur through the action of environmental factors, lifestyles, psychological factors, inflammatory parameters and oxidative stress molecules predisposing to EVA has not been adequately studied. It is also not known which measure of arterial stiffness is best related to EVA.^40^
^41^
^43^ Thus, this study aims to provide evidence to clarify the influence and the relative weight of each of the factors on EVA, assessed using different tools measuring arterial ageing.^11^
^12^

The benefits of moderate physical activity on arterial stiffness, and therefore on EVA, are well known.^15^ Similarly, the number of hours dedicated to sedentary activities is associated with increased stiffness of the large elastic arteries and poorer vascular endothelial function.^17^ However, the effect of endurance exercises, alone or combined with aerobic exercises, on vascular ageing is not clear.^17^

The Mediterranean diet,^27^ accompanied by caloric restriction, improved vascular structure and function.^26^ However, the dietary parameters associated with decreased EVA are not known.

Patients with depression,^28^ anxiety disorders^34^ or subjected to greater stress at work, stress at home, general stress and permanent stress^35^ have a greater risk of suffering CVD. However, we found no studies analysing the association of these factors with EVA. We hope this study will help clarify their influence on EVA.

It is known that smoking is harmful and that low or moderate alcohol consumption has a beneficial effect on CVD. Nevertheless, the weight they have on EVA has yet to be established.

We think that the project we are proposing has national and international relevance: the study of ageing and CVD has been established as a priority line of research in Europe and in Spain. To the best of our knowledge, there is no project in Spain or worldwide analysing in a population sample the majority of the potential factors currently known to influence EVA and attempting to quantify the weight and relevance of each of them. Therefore, we think that this is an original project and given the high prevalence of ageing of the population in our setting, a study to analyse the factors involved in arterial ageing will facilitate an understanding of this phenomenon and the degree of involvement of each factor in this process. In addition, it will provide knowledge for future research lines and potential clinical strategies.

